### Data collection

Pre- and post-assessments will be performed with data collected on:a) Audio recordings (ARs) of real-time communication between older persons and NAs during home care visits before and after the intervention, e.g., 1 plus 1 per NA;b) a questionnaire on self-efficacy communication skills, PCC, empathy, and job satisfaction;c) user data, evaluation form, field notes, observations, and;d) interviews.

To evaluate the effect of the intervention on NAs’ communication, data will be collected by ARs and questionnaires. ARs are considered important data sources when conducting in-depth analyses of interpersonal communication [38]. ARs of real-time communication allow for the collection of empirical data on authentic communication during home care visits, which makes it possible to capture communication in its natural context. Such observations are suggested as an efficient and highly valued method for data collection that can facilitate powerful data and provide new insights into communication in nursing practice, different from interviews where gaps may occur between what people report and recall about communication and behaviours during nursing care [39]. Hence, a strength in ACTION is the evaluation of the actual communication by ARs. There are, however, challenges when recording actual situations. For example, participants may be aware of being recorded and change their behaviour [40], but no major differences have previously been observed [41, 42]. It is the NAs who handle the ARs themselves, no researchers will be present during the home care visits. In order to do this, the NAs will receive thorough information on how to handle the ARs.

All NAs are also expected to complete questionnaires on self-efficacy of communication skills, PCC, empathy, and job satisfaction (see Table 1). Participants in the control group will be asked to complete the same measures at approximately the same time.

**Table 1 Tab1:** Questionnaires used in the ACTION programme

Questionnaire	Items and scale	Focus
Self-efficacy questionnaire (SE-12) [43]	12 items 10-point Likert scale	Confidence in clinical communication skills of healthcare professionals
Person-centred Care Assessment Tool (P-CAT) [44]	13 items 5-point Likert scale	Nursing staff rating the extent of person-centred care in care settings
Jefferson Scale of Empathy (JSE) (Health-provider version) [45]	20 items 7-point Likert Scale	Empathy among health professionals in clinical practice
Measure of Job Satisfaction [46]	38 items 5-point Likert scale	Job satisfaction among nurses: Personal Satisfaction; Satisfaction with Workload; Satisfaction with Professional Support; Satisfaction with Pay and Prospects; and Satisfaction with Training

Data collected with interviews, field notes, and observations will contribute qualitative aspects and experiences during implementation and are important for identifying and resolving potential problems. To evaluate the benefits and potential barriers to implementing competence development in person-centred communication with NAs in home care, we will collect user data on NAs’ participation from the web-based platform, anonymous evaluation forms, field notes and observations. An example of user data is information about when and for how long the NA has visited the learning platform. This will be done by monitoring information logs available through the learning platform and written evaluations from the NAs. Only the researchers within the ACTION programme will have access to the information logs. No information regarding the NAs' participation in the learning platform will be shared with their employers or any other unauthorised person. Field notes and observation notes will be written by the researchers for documenting the implementation process, for example, any strengths or weaknesses in the design or content of the learning modules, the ease of use of the digital learning platform, unforeseen challenges that may arise and important lessons learned for future educational interventions. No personal information about the NAs will be kept in the field or observation notes.

In addition, older persons’ perceptions about NAs’ person-centred communication skills will be collected through individual semi-structured interviews with 20 older persons receiving home care during the implementation phase. It is difficult to estimate how many participants will be needed, thus, the estimation of 20 older persons may be reduced if saturation is reached [47]. The individual interviews with older persons will contribute information about their experiences of communication with NAs during home care visits.

### Outcome measures

Demographic data on NAs and older persons will be collected. NAs will be asked to self-report characteristics regarding sex, age, native language, and work experience. Older persons recruited for ARs and/or interviews will also be asked to report on sex, age, and native language.

The following measures will be used to evaluate the effect of the intervention on NAs’ communication competence and for process evaluations:

#### Primary outcome measure

a) *Person-centred communication* will be measured with audio recordings of communication during home care visits collected at baseline (e.g., before education) and after education (e.g., 8 weeks later) and analysed and coded by sequences of empathic statements and responses to emphatic opportunities, emotional communication, and degree of person-centredness.i. Emphatic and emotional communication, defined according to empathic opportunities, is described by Suchman et al. [33] and their model of emphatic communication.ii. Emotional communication is coded by the Verona Coding Definitions on Emotional Sequences (VR-CoDES) [48].iii. Degree of person-centred communication coded by the Roter Interaction of Analysis (RIAS) [49].

The coding will be made by two independent coders after training, and interrater reliability will be calculated with Cohen’s kappa coefficient or with Pearson correlation analysis.

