### Settings and samples

Approximately 300 NAs will be recruited for the study. Participants will be randomly assigned to either control (*n* = 150) or intervention group (*n* = 150). The recruitment will be organised into two stages: the first stage will be performed by researchers at University 1 with the recruitment of 75 participants in each group, e.g., intervention versus control group. In the next stage, researchers at University 2 will repeat the procedure with the recruitment of 75 participants in each of the intervention and control groups. The power calculation estimated that a sample size of 115 NAs was needed in each group to capture a statistically significant difference in outcomes after the intervention, calculated with a rate ratio of 1.5 with 80% power and a Type I error rate of 5%. The estimation of the sample size is based on the hypothesis that NAs in the intervention group will have a greater number of empathic responses after intervention than those in the control group. To account for dropouts, this number was extended to 150 NAs in each group.

Home care units will be recruited based on contacts with managers who are willing to implement the educational programme for NAs at their unit. A researcher from the project will visit the home care units and provide information about the ACTION programme to the NAs. Every NA, at each home care unit, will be offered to participate in the ACTION programme. After informed consent, they will be included. All participating home care units will be blinded, and do not know if their unit will be part of a control or an intervention group. The randomisation is done by recruiting every second unit to the intervention versus the control group, to aim for an even distribution of the number of units in each group. The intervention groups will be offered the education during implementation, and the control groups will be offered the education after completion of all data collection to compensate for their effort to collect data as controls.

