### Analyses and data processing

Data will be analysed with quantitative and/or qualitative methods. Descriptive statistics will be used for participants’ characteristics to present findings of the coding of empathic opportunities, reports on self-efficacy communication skills and job satisfaction, and data on participants' adherence.

For analysis of our primary outcome, we will compare the number of empathic statements and the number of responses to an empathic opportunity with a continuer rather than a terminator, similar to the study by Tulsky et al. [51]. The number will be calculated in pre- and post-assessments and compared between the control and intervention groups. Considerations will be made regarding hierarchical and clustered data, e.g., both the NAs and older persons may be recorded several times. For the analysis of differences between the intervention and control groups, we will consider using a generalised linear model form of regression analysis. For statistical analysis of differences between subgroups, chi-square tests will be used for responses given on nominal scales and independent t-tests or corresponding nonparametric tests if needed for responses given on continuous scales.

For analysis of secondary outcomes, all self-reported measures from the survey will be treated as continuous variables and compared between the intervention and control groups. Descriptive statistics will be used to analyse the answers reported. We will consider subgroup analysis with inferential statistics on differences related to sex, age, and native language. The analysis will follow the same statistical analysis as described above for the primary outcome. All statistical analyses will be two-sided and performed in IBM SPSS Statistics software Version 25.

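### The plan lets Pearson correlation stand alone as the inter-rater reliability measure for the primary outcome coding, although it cannot show a systematic difference between the two coders

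*Protocol article*

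**What the plan says.** In the protocol article, Primary outcome measure, the audio recordings are coded in three ways: by the empathic-opportunity model, by VR-CoDES and by RIAS. On the coders it says: "The coding will be made by two independent coders after training". On reliability it says that "interrater reliability will be calculated with Cohen’s kappa coefficient or with Pearson correlation analysis". It does not say which statistic goes with which coding system, and no other section names a measure of agreement.

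Under Analyses and data processing, the primary comparison is of numbers: "we will compare the number of empathic statements and the number of responses to an empathic opportunity with a continuer rather than a terminator". Under Settings and samples, the trial is sized on a rate ratio of 1.5 for empathic responses. The RIAS section adds that a patient-centredness ratio is calculated from the RIAS codes.

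**The concern.** The primary outcome is a count per recording, compared in level between groups. The coder error that matters most for such an outcome is a difference in level, where one coder credits more empathic statements or continuers than the other throughout. Pearson's r does not change when one coder's values are multiplied by a positive constant or shifted. It is therefore blind to exactly that error.

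This is a stated choice of statistic, not a detail left for later. What is at stake first is the reported reliability, which readers use to judge whether the primary outcome can be trusted. A second, conditional stake is the treatment comparison, if the two coders do not cover the arms and time points evenly.

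**Working it through.** **Inputs from the article.** There are two coders, the endpoint is a count, and the planned rate ratio is 1.5. The article gives no reliability figure to reproduce. It also gives no mean count and no dispersion. For that reason its 115 per group can be neither confirmed nor refuted. Under a Poisson model, n = (1.960 + 0.842)² × (1/m₀ + 1/(1.5 m₀)) / (ln 1.5)² equals 115 at a control mean m₀ of about 0.69. Overdispersed counts with higher means also reach 115, for example mean 2 with k about 0.79. The means and dispersions below are therefore assumptions, shown as a range.

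**Formulas.** Let coder A's count x have mean μ and variance σ² = μ + kμ².

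- Coder B = c·x: r = 1, and agreement = 2cσ² / [(1 + c²)σ² + (c − 1)²μ²]. At c = 1.5 this is 3σ² / (3.25σ² + 0.25μ²).
- Coder B = x + d: r = 1, and agreement = 2σ² / (2σ² + d²). Here d = 0.5μ, which also makes the coder means differ 1.5-fold.

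These are concordance correlations. With many recordings they coincide with the two-way single-rater absolute-agreement ICC. Simulation of 200,000 recordings per scenario gave the same values to within 0.001.

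| Assumed μ, k | σ² | Pearson r | ICC, B = 1.5x | ICC, B = x + 0.5μ |
|---|---|---|---|---|
| 1, 0.5 | 1.5 | 1.00 | 4.5/5.125 = 0.88 | 3/3.25 = 0.92 |
| 2, 0.5 | 4 | 1.00 | 12/14 = 0.86 | 8/9 = 0.89 |
| 2, 1 | 6 | 1.00 | 18/20.5 = 0.88 | 12/13 = 0.92 |
| 5, 0.5 | 17.5 | 1.00 | 52.5/63.125 = 0.83 | 35/41.25 = 0.85 |
| 5, 0 (Poisson) | 5 | 1.00 | 15/22.5 = 0.67 | 10/16.25 = 0.62 |
| 10, 0 (Poisson) | 10 | 1.00 | 30/57.5 = 0.52 | 20/45 = 0.44 |

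Agreement runs from about 0.45 to 0.92. The value r = 1 does not depend on the assumptions.

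**Differences that are not constant.** Suppose coder B adds an extra count to each of A's with probability one half. Then r is 0.949 to 0.984 and the ICC is 0.50 to 0.86 over the same scenarios. Suppose instead that B misses each of A's events with probability one third. Then r is 0.815 to 0.935 and the ICC is 0.48 to 0.84. In both cases r falls only because of the random scatter; the difference in level does not lower it.

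**Kappa under the same bias.** Let A assign a binary code with prevalence p, and let B assign it to the same events and more, with prevalence 1.5p. Observed agreement is 1 − 0.5p, and chance agreement is 1.5p² + (1 − p)(1 − 1.5p). At p = 0.2, kappa = (0.90 − 0.62)/(1 − 0.62) = 0.74. At p = 0.3, 0.4 and 0.5 it is 0.69, 0.62 and 0.50. Kappa responds to the bias.

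**Effect on the group comparison.** If the higher-counting coder handles a share s of an arm's recordings and counts 1.5-fold, that arm's mean is multiplied by 1 + 0.5s. With no true effect, the ratio between arms is:

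- 50/50: 1.25/1.25 = 1.00
- 60/40: 1.30/1.20 = 1.08
- 75/25: 1.375/1.125 = 1.22
- one arm each: 1.50/1.00 = 1.50

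**The case against.** The strongest reply is that the article never assigns Pearson to the primary counts. Kappa is named first. The empathic-opportunity terms and VR-CoDES are categorical at event level, and the primary counts are sums of such events. A fair reading is kappa for those codes and a correlation for the RIAS ratio. In that case a coder bias in the primary codes would show. This stands: that Pearson is meant for the counts is something a reader might infer, not something the text says. What remains is that the wording allows it, and that Pearson is no better suited to the RIAS ratio.

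A reader might also set a 1.5-fold coder difference beside the planned rate ratio of 1.5 and conclude that coder bias could produce the whole target effect. The two ratios coincide only if each coder codes one entire arm, and nothing in the article suggests that. If both coders code everything, or share the files evenly, a constant proportional difference cancels from the ratio.

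Third, an ICC of 0.83 to 0.92 could itself be reported as good, so changing the coefficient is not enough. This also stands, and it shapes the fix. Finally, how files are assigned to coders is commonly left to a full protocol or coding manual. Its absence from a journal article is not a fault.

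**Conclusion.** The point holds as a misspecified reliability measure. The plan's wording permits Pearson alone for counts per recording or the RIAS ratio. A constant 1.5-fold or equivalent additive coder difference would then be reported as r = 1.00, and random over-counting of that size as about 0.95 to 0.98. Absolute agreement for the constant difference is about 0.45 to 0.92. That range rests on assumed means of 1 to 10 and k of 0 to 1.

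The documents do not support a claim that the treatment effect is biased. For a 1.5-fold proportional coder difference, bias arises only if recordings are unevenly divided between coders by arm or time point: 1.08 at 60/40 and 1.22 at 75/25. The article does not state the division. Nor does it make reliability a condition for, or an input to, the primary analysis. The consequence established here is a potentially misleading reliability report.

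**What to change.** In Primary outcome measure, replace the option of Pearson correlation with a rule by type of measure:

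- Cohen's kappa for the categorical event-level codes.
- For counts per recording and the RIAS ratio, a two-way, single-rater, absolute-agreement ICC (or the concordance correlation), always reported with the mean coder difference or ratio.

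The second element of that report is essential, because the ICC can stay above 0.8 under a 1.5-fold bias whereas the mean ratio shows the bias directly. Together with the record of who coded which files, it also lets a reader gauge any effect on the group comparison.

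The cost is a change of wording. The same double-coded recordings are used, with no further coding or data collection.

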#### Secondary outcome measures

b) *Communication skills* [43]*, Person centred care* [44]*, Empathy* [45], and *Job satisfaction* [46] will be measured with questionnaires at baseline (e.g., before education) and after education (e.g., 8 weeks later).c) *Process evaluation* will be conducted with interviews, evaluation forms, field notes, and observations during the education with a focus on qualitative aspects and experiences of the implementation, weekly at weeks 1–6 during the education.d) Older persons’ *perceptions about the meaning of and experiences with* NA’s person-centred communication will be measured with interviews, at weeks 6–8.

### Coding systems and questionnaires

#### Empathic opportunities

The coding system defines terms for describing patients’ expressions of emotions and the provided response from the healthcare provider. There are seven defined terms: empathic opportunities, empathic response, empathic opportunity terminator, missed empathic opportunity, potential empathic opportunity continuer, and potential empathic opportunity terminator [33, p.679]. In addition, opportunities for praise can be defined in terms of praise opportunity, praise, and praise opportunity terminator [33, p.681].

#### VR-CoDES

VR-CoDES can be used for coding opportunities of emotional communication in ARs by coding patients’ utterances of emotional distress and the healthcare providers' responses to these utterances. The coding system contains detailed codes for both utterances of emotional distress and subsequent responses to these utterances. Emotional distress is coded either as a clear expression of an emotional concern or as an implicitly expressed cue of a patient’s emotional distress, and there are seven definitions of cues [48]. After a concern/cue, the healthcare providers’ response is coded, either as an explicit or nonexplicit response, which provides or reduces space for further disclosure and is then divided into further definitions of response categories (a total of 17 categories) [50].

#### RIAS

Originally, RIAS was constructed to code medical dialogue, but it has been widely used in other areas of communication research [49]. RIAS focuses on establishing task-focused and socioemotional elements in communication. These elements are established by assigning codes to the communication. From the coded elements, a ratio of patient-centeredness, in the communication, can then be calculated. RIAS has a total of 40 codes, which are applied to the smallest unit of expression to which a code can be assigned, for example, a sentence, a section of a sentence, or a single word.

#### Questionnaires

In addition to demographic data about the participants, surveys obtained through questionnaires will contribute self-reported information regarding communication skills and abilities, empathy, and job satisfaction. All questionnaires have been validated and used in other studies and are published elsewhere. Please see Table 1 for information regarding the questionnaires in the ACTION programme.

### Analyses and data processing

Data will be analysed with quantitative and/or qualitative methods. Descriptive statistics will be used for participants’ characteristics to present findings of the coding of empathic opportunities, reports on self-efficacy communication skills and job satisfaction, and data on participants' adherence.

For analysis of our primary outcome, we will compare the number of empathic statements and the number of responses to an empathic opportunity with a continuer rather than a terminator, similar to the study by Tulsky et al. [51]. The number will be calculated in pre- and post-assessments and compared between the control and intervention groups. Considerations will be made regarding hierarchical and clustered data, e.g., both the NAs and older persons may be recorded several times. For the analysis of differences between the intervention and control groups, we will consider using a generalised linear model form of regression analysis. For statistical analysis of differences between subgroups, chi-square tests will be used for responses given on nominal scales and independent t-tests or corresponding nonparametric tests if needed for responses given on continuous scales.

For analysis of secondary outcomes, all self-reported measures from the survey will be treated as continuous variables and compared between the intervention and control groups. Descriptive statistics will be used to analyse the answers reported. We will consider subgroup analysis with inferential statistics on differences related to sex, age, and native language. The analysis will follow the same statistical analysis as described above for the primary outcome. All statistical analyses will be two-sided and performed in IBM SPSS Statistics software Version 25.

Data on field notes and reports from participants will be collected as text, and each interview will be transcribed before analysis. Both field notes, interviews, and reports will be analysed qualitatively with content analysis [52]. The content analysis will be inductive and grounded in the actual data, i.e., conventional content analysis. Conventional content analysis is appropriate when previous research or theories are limited. The data will be read several times to gain a sense of the whole. The content will then be organised into codes and sorted into categories according to differences and similarities that emerge from the data. Exemplars for each category will be presented when reporting the results. The advantage of using conventional content analysis is that the information is gained directly from the data without interpretation, theoretical perspectives, or predetermined categorisations [52].

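### The analysis does not commit to accounting for the home care unit, although the unit is what is allocated

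*Protocol article*

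**What the plan says.** **Allocation (Protocol article, Settings and samples).** The operational description is by unit: "The randomisation is done by recruiting every second unit to the intervention versus the control group". Blinding is also described by unit, since units "do not know if their unit will be part of a control or an intervention group". Recruitment takes in whole units: "Every NA, at each home care unit, will be offered to participate in the ACTION programme". The same section nevertheless words the assignment as individual: "Participants will be randomly assigned to either control" or intervention group.

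**Analysis (Protocol article, Analyses and data processing).** The clustering sentence reads: "Considerations will be made regarding hierarchical and clustered data, e.g., both the NAs and older persons may be recorded several times". For the comparison of intervention with control, "we will consider using a generalised linear model form of regression analysis". A separate sentence, on differences between subgroups, names chi-square tests for nominal responses and "independent t-tests or corresponding nonparametric tests if needed for responses given on continuous scales". The questionnaire outcomes are to be analysed in the same way as the primary outcome. The home care unit does not appear anywhere in this section.

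**Sample size (Settings and samples).** "The power calculation estimated that a sample size of 115 NAs was needed in each group", based on a rate ratio of 1.5, 80% power and a 5% type I error rate, then raised to 150 per group for dropout. No ICC, number of units, unit size or design effect is mentioned.

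**The concern.** When whole units go to one arm, the variation between units enters the standard error of the intervention effect. Modelling repeated recordings of the same NA or older person does not capture it. The data collection section gives one recording before and one after per NA, so the clustering named for NAs is mainly the pre-post pair. The clustering that the allocation itself creates is not named.

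Correlation within units is plausible here. P-CAT asks staff to rate how person-centred the care setting is, so colleagues rate a shared object. The job satisfaction measure covers workload and professional support, which are largely features of a workplace. The programme includes on-site group supervision and local facilitators, which could add correlation in the intervention arm.

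At stake is the 5% error rate for the primary outcome and, because the same analysis is carried over, for the questionnaires. An analysis that follows this text to the letter could leave the unit out and report p-values that are too small and intervals that are too narrow.

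**Working it through.** **1. What is allocated.** Alternation by unit, blinding by unit and an invitation to every NA in the unit all mean that colleagues share an arm. The sentence on randomly assigned participants points the other way. The working below takes the operational description, allocation by unit.

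**2. The plan's own figure.** For a two-group Poisson comparison with independent NAs and a two-sided test:

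n per arm = (1.960 + 0.842)² × (1/λ₀ + 1/(1.5 λ₀)) / (ln 1.5)²

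The control-group mean count λ₀ is not stated, so 115 cannot be verified. It is returned when λ₀ is about 0.69 empathic responses per recording (λ₀ = 0.5 gives 160, λ₀ = 1 gives 80). With overdispersion, 115 is also reached at λ₀ = 1 with a negative binomial dispersion of 0.37. So 115 is attainable with independent NAs, without any design effect.

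**3. Effect of leaving the unit out.** With m NAs per unit and intracluster correlation ICC:

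- design effect DE = 1 + (m − 1) × ICC
- true two-sided alpha of a nominal 5% test that ignores units = 2 × (1 − Φ(1.96/√DE))
- factor by which intervals are too narrow = √DE

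The documents give neither m nor ICC. All values of both below are assumptions. For scale, 115 NAs per arm means 23 units per arm at m = 5, 11.5 at m = 10, 10 at m = 11.5 and 6 at m ≈ 19.2.

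| ICC (assumed) | m (assumed) | DE | True alpha | √DE |
|---|---|---|---|---|
| 0.01 | 5 | 1.04 | 5.5% | 1.02 |
| 0.01 | 10 | 1.09 | 6.0% | 1.04 |
| 0.05 | 10 | 1.45 | 10.4% | 1.20 |
| 0.05 | 11.5 | 1.525 | 11.2% | 1.23 |
| 0.05 | 20 | 1.95 | 16.0% | 1.40 |
| 0.10 | 19.2 | 2.82 | 24.3% | 1.68 |

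Example: at m = 11.5 and ICC 0.05, DE = 1 + 10.5 × 0.05 = 1.525. Then 1.96/√1.525 = 1.587, and 2 × (1 − Φ(1.587)) = 0.112.

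Over m = 5 to 30 and ICC 0.01 to 0.10, true alpha runs from 5.5% to 32%.

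**The case against.** The strongest reply is that the text is open rather than wrong. It speaks of hierarchical as well as clustered data, and its example is introduced by e.g., so the list is not exhaustive. A generalised linear model can be fitted with GEE, random effects or a cluster-robust variance, and a statistical analysis plan may settle this. That stands: the documents do not exclude a unit term. What remains is that the article chooses to discuss clustering, illustrates it with another level, promises only unspecified considerations, and leaves out the level fixed by its own allocation.

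A reader might infer that chi-square and independent t-tests are a fallback for the primary comparison. The text does not support this. It assigns them to differences between subgroups, and a separate sentence covers intervention against control. The wording is loose enough that they could reach the questionnaires, and as subgroup tests they still assume independent NAs, but no fallback for the primary comparison is stated.

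The size is also open to challenge. At ICC 0.01 with small units the distortion is minor. The outcome is measured before and after, and adjusting for baseline, if done, would usually lower the residual correlation within units. The ICC that matters is that residual one, and the documents do not give it.

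**Conclusion.** The point holds in conditional form. The article describes allocation by home care unit, and its analysis section does not commit to accounting for the unit, for either the primary or the questionnaire outcomes. If the unit is ignored and the unit ICC is above zero, inference is anti-conservative. The excess is slight at the bottom of the assumed range (true alpha 5.5-6%), about double the nominal level in the middle (10-11%), and about 24% at ICC 0.10 with about 19 NAs per unit.

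A reader might infer that the results will necessarily be too optimistic. The documents do not establish that, because it depends on the final model and on an ICC and unit size that are not stated. The calculation also assumes units of equal size and a normal approximation. The contradiction between individual assignment and alternation by unit needs resolving in any case, because it decides which level the analysis must respect.

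**What to change.** 1. Reconcile the two allocation statements in Settings and samples, so that the unit of allocation is unambiguous.
2. In Analyses and data processing, name the home care unit as a cluster level in the intervention-control comparison, for the primary outcome and all questionnaire outcomes. A mixed model with a random intercept for unit, or GEE with the unit as cluster, would serve. A negative binomial mixed model is one acceptable choice for the counts, not the only one. State a small-sample correction, since units may be few, and confirm that the named software can fit the chosen model with it.
3. Replace independent chi-square and t-tests for subgroups with tests that respect the same structure, for example intervention-by-subgroup terms in that model.

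The cost is wording, slightly more analysis work and wider intervals: by a factor of about 1.20-1.23 at ICC 0.05 with 10-11.5 NAs per unit. The wider intervals also reduce power. Using Φ(2.80 × √(n/115)/√DE − 1.96), power at 115 per arm falls from 80% to about 77% (m = 10, ICC 0.01) or 64% (m = 10, ICC 0.05). At 150 per arm with no dropout it would be about 87% and 76%. These figures rest on the same assumptions, and it is better to know them before the analysis.
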